#### Mediators/predictors

All participants complete a demographic questionnaire at assessment/baseline. Additionally, in order to evaluate whether changes in young people’s levels of psychological distress is mediated by the quality of the relationship that they have with a professional (either counsellors or pastoral care teachers), and/or the quality of the alliance that they experience with their counsellor (for those allocated to SBHC), at mid-point/6 weeks we administer mediating/process measures of ‘Rogerian’ conditions (using the Barrett-Lennard Relationship Inventory Student Form (BLRI OS-40 T-S), [54] in both groups; and the therapeutic alliance (using the WAI-S [42]) in the SBHC group.

Counsellors and supervisors complete demographic questionnaires developed for the study. A researcher completes a School Characteristics Form, developed for the study, with a member of the school’s pastoral care team. This is to obtain data on the size and type of school, pastoral care provision, and characteristics of the general school population.

In the SBHC group, in the first counselling session, the counsellor completes the Current View [55] to record the young person’s characteristics and their presenting issues.

Adherence to the SBHC model is also measured (see above).

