#### Adverse event monitoring

Individuals in contact with trial participants (including pastoral care staff, assessors, counsellors (and their supervisors) testers and qualitative interviewers) are required to use an Adverse Events (AEs) Reporting Log to record the occurrence of any AE in a trial participant throughout the trial (see below).

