#### Analysis of clinical effectiveness

The primary analysis will be based on the intention-to-treat principle. Per-protocol analysis will also be conducted. Baseline characteristics will be described by group and pooled using mean, standard deviation (SD), minimum, maximum, median, and interquartile range. Categorical variables will be described by frequency. Analyses will be performed using linear mixed-effects models (LMMs) including data from all randomised participants by intention to treat. All variables used for stratification/minimisation will be included as covariates (random intercept for school and practitioner; fixed effect for other baseline characteristics). Differences between SBHC and PCAU will be summarised by 95% CIs of the difference between groups, estimated by the LMMs. Given the likely non-linear patterns of change and measures taken at discrete time points, analyses will be conducted at each time point, adjusted by baseline scores. Standardised mean differences will be calculated using the LMM-estimated mean differences between groups at each time point after baseline, divided by the baseline SD. Sensitivity analyses will be conducted to test for any moderating effects of support provided to participants to complete measures. Participants with and without missing data will be compared using baseline characteristics, including intervention allocation, to test for patterns of missing values and systematic biases. Multivariate imputation by chained equations will be used to compute questionnaire scores for participants with missing item responses.

Secondary analysis will include modelling of the extent to which the relationship between intervention allocation and outcome is mediated by the BLRI variables, and testing for differences in the frequency of AEs by allocation. Data will also be analysed within the treatment group to determine whether outcome is predicted by mid-point therapeutic alliance, while adjusting for all baseline variables.

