### Risk procedures and reporting of adverse events (AEs)

Written protocols for managing risk, and monitoring and reporting AEs and serious adverse events (SAEs) is followed for all trial participants throughout the trial (from the point of enrolment into the trial, to the follow-up/24-week time point). An adverse event (AE) is defined as any negative psychological, emotional or behavioural occurrence, or sustained deterioration in a research participant. In the current trial, we have included arrest by police; running away from home; excluded from family home; school exclusion; significant decrease in school attendance; significant deterioration in behaviour, including threatening violence, exhibiting violent behaviour or serious injury to another person, exposure to violence or abuse; significant increase in emotional difficulties; self-harm (if not a presenting issue), or escalating self-harm (when it is a presenting issue); a complaint made against the counsellor, or an issue with the counsellor, resulting in discontinuation of counselling; suicidal ideation; suicidal intent; hospitalisation due to drugs or alcohol, or for psychiatric reasons; and death, including suicide.

An Adverse Events Reporting Form is used by all individuals in contact with participants, who are trained to recognise and respond, in an ethical and timely way, to risk and any issues relating to safeguarding. The overall safety of participants is the responsibility of the trial’s chief investigator (CI). However, in practice the CI relies on all research staff, counsellors, supervisors and school staff to ensure that AEs are identified and addressed in an appropriate and timely manner. Thus, safety is a shared responsibility. Individuals completing the form are asked to consider whether the AE is serious, defined as any AE which is life threatening or results in death, and whether it may be a result of participating in the trial. The severity of each AE is also assessed, according to its intensity, duration and the degree of impairment to the young person (or, when relevant, another person such as in case of risk to others). Severity is graded as ‘mild’, ‘moderate’, ‘severe’, ‘very severe’, or ‘extremely severe’.

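### Adverse event frequency is to be tested between arms, although SBHC participants have extra AE reporters and one listed AE can occur only in SBHC

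*Protocol article*

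**What the plan says.** The protocol article, under Analysis of clinical effectiveness, lists "testing for differences in the frequency of AEs by allocation" among the secondary analyses. It sets no limit on who reported the event or on which AE categories count.

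Two sections say who reports. Adverse event monitoring requires everyone in contact with a participant to log any AE, "including pastoral care staff, assessors, counsellors (and their supervisors) testers and qualitative interviewers". Risk procedures and reporting of adverse events adds that "An Adverse Events Reporting Form is used by all individuals in contact with participants" and that in practice "the CI relies on all research staff, counsellors, supervisors and school staff to ensure that AEs are identified" and dealt with. The same section sets the AE window from enrolment to the 24-week follow-up, and its list of AEs includes "a complaint made against the counsellor, or an issue with the counsellor, resulting in discontinuation of counselling".

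Contact differs by arm:

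- **SBHC** (Delivery of SBHC): up to ten weekly individual sessions of 45 to 60 minutes, with the school's pastoral care still available.
- **PCAU** (Control group): existing school support without humanistic counselling. SBHC is offered 6 to 9 months after assessment.
- **Interviews** (Qualitative interviews): held at 12 weeks, with a target of 50 young people, all from the SBHC group.

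**The concern.** When everyone who meets a pupil is a reporter, the number of recorded AEs depends on how often the pupil is seen and by whom, as well as on how often events happen. Counsellors are trained to recognise risk, and they hear private accounts of distress for up to ten sessions. They are well placed to learn of suicidal ideation, self-harm or exposure to abuse, all of which are on the AE list. Within the AE window they see one arm only.

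The counsellor-complaint category is a separate problem. Its expected count in PCAU is zero by definition, so including it adds events to one side whatever the detection rates are.

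A test on such counts can return a difference when true harm is equal, or hide a real reduction under SBHC. In a trial of distressed adolescents, an apparent excess of self-harm or suicidality under counselling would carry weight with readers and policy-makers.

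**Working it through.** **Sources by arm within the window.** The PCAU offer of SBHC starts at 6 months. The AE window closes at 24 weeks, and 24 / (52/12) = 5.5 months. PCAU pupils therefore have no counsellor reporter inside the window.

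| Reporter | SBHC | PCAU |
|---|---|---|
| Assessors; testers at 6, 12 and 24 weeks | yes | yes |
| Pastoral and other school staff | yes | yes |
| Counsellor, up to 10 sessions | yes | no |
| Supervisor (mostly through the counsellor) | yes | no |
| Interviewer of pupils (target 50) | yes | no |

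The last two rows are minor. Supervisors learn mainly from counsellors, and one interview with 50 pupils reaches about a third of the arm (50/153 = 33%).

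**Numbers per arm.** The article gives no figure for the AE comparison, so I use its sample size, which reproduces. The design effect is 1 + (7.2 - 1) x 0.05 = 1.31. Then 1.31 x 86 = 112.66, rounded to 113; 113/7.2 = 15.7, rounded to 16; add 1 for 17 counsellors; 17 x 9 = 153 per arm, 306 in total.

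**Illustration of unequal detection.** The article gives neither AE risk nor detection rates. These inputs are assumptions:

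- true risk per participant p = 0.20 or 0.40, equal in both arms;
- detection by common sources b = 0.5 to 0.7;
- share of the remainder picked up by SBHC-only sources e = 0.3 to 0.5.

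Recorded PCAU risk is p x b. Recorded SBHC risk is p x [b + (1 - b) x e]. The test is a two-sided 5% two-proportion z-test with pooled standard error, 153 per arm, clustering ignored.

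| b | e | Ratio | PCAU v SBHC, p = 0.20 | Rejects | PCAU v SBHC, p = 0.40 | Rejects |
|---|---|---|---|---|---|---|
| 0.7 | 0.3 | 1.13 | 14.0% v 15.8% | 7% | 28.0% v 31.6% | 11% |
| 0.7 | 0.5 | 1.21 | 14.0% v 17.0% | 11% | 28.0% v 34.0% | 21% |
| 0.5 | 0.3 | 1.30 | 10.0% v 13.0% | 13% | 20.0% v 26.0% | 24% |
| 0.5 | 0.5 | 1.50 | 10.0% v 15.0% | 26% | 20.0% v 30.0% | 52% |

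With equal detection (e = 0) the rate is the nominal 5%.

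**The SBHC-only category alone.** Let detection be equal and let a share q of SBHC pupils incur the counsellor category. Recorded SBHC risk becomes base + q x (1 - base). For q of 1% to 5%, the test rejects in 5.8% to 22% of trials at a base recorded risk of 10%, and in 5.2% to 10% at a base of 30%.

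**Displaced pastoral reporting.** Suppose common-source detection falls in SBHC to b' because counsellors take over some of that contact. The arms balance when b' + (1 - b') x e = b, so b' = (b - e)/(1 - e). In the mildest case, b' = (0.7 - 0.3)/0.7 = 0.57, so a fall from 0.70 to 0.57 would cancel the all-source bias. A test on common sources alone would then compare 0.20 x 0.57 = 11.4% with 14.0%, a ratio of 0.82 in favour of SBHC.

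**The case against.** The strongest reply is that the AE test is one clause in a journal article, that an analysis plan agreed in advance is promised, and that sources and categories are normally settled there. The point, however, is not missing detail. The article states an unrestricted comparison of data that its own procedures collect unequally, and carrying it out as written gives that comparison. An analysis plan could still repair it.

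A second reply is that the direction is likely but not settled. The Background reports a pilot finding that counselling reduced the time form teachers and pastoral staff spent with these pupils, so counsellor reports may partly replace pastoral ones. School exclusion and attendance are known to schools in both arms. This stands, and it limits how firmly the bias can be stated. It also means that a common-source test used alone could err in SBHC's favour.

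Two stronger readings are tempting, but the documents do not support them.

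- **Self-harm and presenting issues.** The AE list counts "self-harm (if not a presenting issue), or escalating self-harm (when it is a presenting issue"), and "In the SBHC group, in the first counselling session, the counsellor completes the Current View" to record presenting issues. A reader might infer that this inflates self-harm AEs in SBHC. Nothing says that the Current View decides AE status. If it did, fuller recording of presenting issues would tend to remove self-harm events from SBHC, because only escalation would then count. Both arms also have a baseline risk discussion and YP-CORE item 4.
- **PCAU contact limited to testers and pastoral staff.** A reader might infer this from the design. The Control group section allows for a school nurse, learning mentor, educational psychologist or behaviour support team, and all individuals in contact with participants use the AE form.

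**Conclusion.** The concern holds as a structural fault. Within 24 weeks, SBHC has a class of AE reporters that PCAU lacks, and one AE category is impossible in PCAU. An unrestricted test will tend to show more recorded AEs under SBHC at equal true harm.

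Its size is unknown. On the assumed detection rates the recorded ratio runs from 1.13 to 1.5, and the false-positive rate from 7% to 26% at a true risk of 20% and from 11% to 52% at 40%. At the mild end the excess over 5% is slight. The model treats counsellor detection as purely additional, and displaced pastoral reporting would shrink or cancel the effect. The counsellor-only category does not depend on detection assumptions, although its contribution depends on how often it occurs.

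This should be changed before the between-arm AE result is interpreted. The sample size is not in question.

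**What to change.** 1. Record the reporter's role for every AE, on the form or from the forms already completed if they identify it.
2. Leave the counsellor-complaint category out of the between-arm test and report it descriptively for SBHC.
3. Prespecify, beside the all-source comparison, a comparison restricted to sources common to both arms: school and pastoral staff, assessors, testers at 6, 12 and 24 weeks, and school records.
4. Tabulate all AEs by source and arm.
5. State in advance that an all-source excess under SBHC will not be read as harm unless the common-source comparison agrees.

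The cost is some analysis wording and one data field. Fewer events enter the common-source test, so it has less power, and it may understate SBHC events if disclosures move from pastoral staff to counsellors. That is why both comparisons are shown. All AEs are still reported, and safety monitoring is unchanged.

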### Blinding

Allocation of each participant to SBHC or PCAU is recorded in a separate Assessment Log used only by the assessors. Blinding of participants, providers and assessors is not possible, so this trial employs a ‘tester blind’ design wherein testers are blind to the young person’s allocation for the duration of the trial. To help ensure the success of the blind, a different tester is employed at 6 weeks/mid-point, 12 weeks/endpoint and 24 weeks/follow-up for each participant. The success of the blind is assessed by asking testers to report whether the participant or member of the pastoral care staff have revealed what group the participant is allocated to, on the predesigned Case Report Form (CRF) developed for the trial. Participants and school staff are asked not to reveal the group to which participants have been assigned, as far as is possible.

It is necessary to unmask the allocation of participants to testers conducting the mid-point/6-week meeting to allow the administration of the Working Alliance Inventory Short Form (WAI-S) [42] in the SBHC group (see below, ‘Measures’). Therefore, three separate CRFs have been developed at the mid-point/6-week meeting to ensure that the remaining measures are administered under blind conditions: CRF 1 contains all measures for administration to both groups and is used in the first part of the meeting, CRFs 2 and 3 contain measures only applicable to the SBHC or PCAU group, respectively, and are used in the second part of the meeting. Once CRF 1 has been completed by the participant, the participant’s allocation is revealed to the tester who opens a sealed envelope containing information as to which group the participant is in, and which CRF (2 or 3) should, therefore, be administered. Only testers conducting the mid-point/6-week test have access to the contents of the envelope, which is destroyed following use. The only measures completed following the unmasking of the tester are those relevant to the participant’s specific allocation.

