#### Primary outcomes

##### Young Person’s Clinical Outcomes in Routine Evaluation (YP-CORE)

The primary outcome measure is the YP-CORE [34], a 10-item, self-report, 5-point Likert-type scale measuring psychological distress. Participants are asked to rate how they have been feeling over the last week (prior to completing the questionnaire) in relation to 10 items. Individual item scores range from 0 (‘not at all’) to 4 (‘most or all of the time’) with a total YP-CORE score ranging from 0 to 40. The YP-CORE was chosen because it is a clinically relevant measure to assess changes in psychological distress in the age group being studied in the current trial, and because it has demonstrated internal reliability (*α* = 0.80) and test-retest reliability across 1 week (*r* = 76, 95% CI 0.65 to 0.86) [34]. The YP-CORE is administered at assessment/baseline, mid-point/6 weeks, endpoint/12 weeks, and follow-up/24 weeks.

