#### Secondary outcomes

A range of secondary, self-report outcome measures is collected in both groups. At assessment/baseline, mid-point/6 weeks, endpoint/12 weeks, and follow-up/24 weeks the SDQ [35] is collected to measure psychological difficulties, the Revised Children’s Anxiety and Depression Scale–Short Version (RCADS-SV) [48] collects data on depression and anxiety, the Rosenberg Self-esteem Scale (RSES) [49] collects data on self-esteem, the Student Engagement Scale–Behavioral Engagement sub-scale (SES-BE) [50] collects data about behavioural engagement at school, the Warwick-Edinburgh Mental Well-being Scale (WEMWBS) [51] collects data about level of well-being, and the Goal Based Outcome Record Sheet (GBORS) [52] measures degree of attainment towards personal goals. In addition, at endpoint/12 weeks, the Experience of Service Questionnaire (CHI-ESQ) [53] is administered to measure satisfaction with treatment provision. At the start of each counselling session, participants in the SBHC group are asked to complete the Outcomes Rating Scale (ORS) which assesses areas of life functioning known to change as a result of a therapeutic intervention [39].

In addition, at assessment/baseline and the follow-up/24-week point, schools provide data for educational indicators for each participant in the trial. This will include attendance rate, exclusion rate, detentions and disciplinary proceedings over the previous 3 months as well as current grades.

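### The alliance–outcome model adjusts for baseline only and so can pick up early improvement; a second model with 6-week YP-CORE should be reported beside it

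*Protocol article*

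**What the plan says.** *Analysis of clinical effectiveness* describes a secondary analysis confined to the SBHC arm: "Data will also be analysed within the treatment group". Its question is "whether outcome is predicted by mid-point therapeutic alliance, while adjusting for all baseline variables". Population, predictor and adjustment set are therefore stated. No covariate measured after baseline is named, and the time point of the outcome is not given.

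*Mediators/predictors* says "at mid-point/6 weeks we administer mediating/process measures of" relationship conditions in both arms, and of "the therapeutic alliance (using the WAI-S [42]) in the SBHC group". The purpose given there is to learn whether change in distress is mediated by the relationship with a professional "and/or the quality of the alliance that they experience with their counsellor". *Aims* includes identifying mechanisms of change.

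On the outcome: "The YP-CORE is administered at assessment/baseline, mid-point/6 weeks, endpoint/12 weeks, and follow-up/24 weeks". *Blinding* gives the order at the 6-week meeting: "CRF 1 contains all measures for administration to both groups and is used in the first part of the meeting". Allocation is then revealed and the arm-specific form follows, which for SBHC holds the WAI-S. YP-CORE is collected in both arms, so it belongs to the first form. Counselling runs over ten school weeks (*Delivery of SBHC*), so part of it may already have been delivered by week 6.

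**The concern.** The comparison is between SBHC participants who rate the alliance high and those who rate it low. Nobody is randomised to alliance, so everything depends on the adjustment set. Two routes could link 6-week alliance with 12-week YP-CORE. A good alliance may bring about improvement. Or a young person who is already better by week 6 may rate the alliance more favourably and then stay better. Baseline adjustment cannot deal with the second route, because that improvement happens after baseline. The score that would help to separate the two is taken earlier at the same meeting and is not in the stated model. If the outcome were also taken at week 6, predictor and outcome would be concurrent, with the outcome completed first.

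At stake is a statement about mechanism. The randomised comparison, its sample size and the primary result are not affected.

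**Working it through.** **Number analysed.** The plan gives no figure for the alliance analysis, but its sample size fixes the arm. Two-sample t-test, SMD 0.5, 90% power, 5% two-sided (alpha is not stated; assumed, in line with the 95% CIs): 86 per arm, as in *Sample size*. Design effect 1 + (7.2 − 1) × 0.05 = 1.31; 86 × 1.31 = 112.7, so 113; 113/7.2 = 15.7, so 16; plus 1 = 17; 17 × 9 = 153 per arm, 306 in total. This reproduces the plan. With 20% loss, 153 × 0.8 = 122.4, so n ≈ 122.

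**Assumptions, not in the documents.** Alliance has no effect on 12-week YP-CORE. Its partial correlation with 6-week YP-CORE given baseline is −q. Three sets of YP-CORE correlations cover weaker to stronger tracking. Counsellor clustering is ignored.

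**Formulas.**
- Tracking given baseline: ρ = (r₆,₁₂ − r₀,₆ r₀,₁₂) / √[(1 − r₀,₆²)(1 − r₀,₁₂²)]. Middle set: (0.6 − 0.5 × 0.4)/√(0.75 × 0.84) = 0.50.
- Spurious partial correlation in the baseline-only model: −qρ. For q = 0.3, middle set: −0.15.
- Rejection rate: z = atanh(qρ) × √(122 − 4); Φ(z − 1.96) + Φ(−z − 1.96). For q = 0.3, middle set: z = 1.65, rate 38%.

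**Baseline-only model, rejection rate with no alliance effect:**

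| Correlations 0–6 / 6–12 / 0–12 weeks | ρ | q = 0.1 | 0.2 | 0.3 | 0.4 |
|---|---|---|---|---|---|
| 0.4 / 0.5 / 0.3 (weaker) | 0.43 | 8% | 16% | 30% | 48% |
| 0.5 / 0.6 / 0.4 (middle) | 0.50 | 9% | 20% | 38% | 60% |
| 0.5 / 0.7 / 0.45 (stronger) | 0.61 | 10% | 27% | 53% | 78% |

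Simulation with ordinary least squares (4,000 data sets per setting) agrees: for q = 0.2, 0.3 and 0.4 it gives 14%, 30%, 48% (weaker), 20%, 39%, 60% (middle) and 27%, 53%, 78% (stronger). In the middle set it gives 9% at q = 0.1 and 4.9% at q = 0. With 6-week YP-CORE added, the rate is 4.6% to 5.5% throughout, provided that score is free of error.

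**Allowing for error in the 6-week score.** The YP-CORE section gives internal reliability 0.80 and a one-week test–retest correlation printed as 76, read here as 0.76. Let a be the observed alliance–distress correlation at week 6 and t = 0.6 the tracking to week 12, both given baseline. Assume that the reliability λ applies to these residuals and that alliance and the 12-week score both follow the true state at week 6. The alliance–12-week correlation is then at/λ in size, and after adjustment for the observed 6-week score it is (at/λ − at)/√[(1 − a²)(1 − t²)]. Rejection rates use √118 and √117 respectively.

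| a | λ | at/λ | Baseline-only | Adjusted r | Adjusted |
|---|---|---|---|---|---|
| 0.3 | 0.80 | 0.225 | 70% | 0.059 | 10% |
| 0.3 | 0.76 | 0.237 | 75% | 0.074 | 13% |
| 0.4 | 0.80 | 0.300 | 92% | 0.082 | 14% |
| 0.4 | 0.76 | 0.316 | 94% | 0.103 | 20% |

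Adjustment removes most of the inflation, but not all of it.

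**Reversed arrow.** Suppose instead that alliance truly lowers 6-week YP-CORE (−0.3) and that this carries to week 12 (0.6), with no measurement error. The three correlations are the same as under reverse causation, so the baseline-only model rejects in 51% (z = atanh(0.18) × √118 = 1.98) and the adjusted model in 5%. Neither model alone tells the two situations apart.

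**The case against.** The planned sentence asks about prediction, and for prediction the baseline-adjusted model is sound: alliance that follows early gain does predict later outcome. That stands, and it is why the planned model should be kept. It does not settle the matter, because *Mediators/predictors* and *Aims* give mediation and mechanism as the purpose, and a prediction model does not support that use.

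The choice can also be called one between two estimands rather than between wrong and right. The reversed-arrow calculation bears this out: adding 6-week YP-CORE would erase a real effect that acted before week 6. This also stands, and is the reason for reporting both models.

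A reader might infer that the trial will report early improvement as an effect of alliance. The documents do not support that. Nothing in them shows that improved participants rate the alliance higher, and the correlations are assumptions.

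A reader might extend the point to the BLRI mediation analysis. The protocol states no adjustment set or outcome time for it, and that detail can be left to the analysis plan. A reader might also object that adjusting for every baseline variable over-fits. The protocol does not count those variables, so the charge cannot be quantified, and any particular shorter list would be a preference.

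**Conclusion.** The point holds in a limited form. The protocol itself fixes baseline-only adjustment for a non-randomised, within-arm analysis meant to inform mechanism, while a score that bears directly on the main alternative explanation is collected earlier at the same meeting. Under the assumptions above, an alliance–outcome association can then appear without an alliance effect in roughly 9% to 78% of trials with moderate to strong tracking (8% to 48% with weaker tracking), against a nominal 5%. There is no inflation if alliance is unrelated to early change. The width of the range reflects inputs that the documents do not give, so no single figure should be quoted as the error rate.

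It would also go too far to say that adding 6-week YP-CORE restores 5%. That needs an error-free score; with the reliabilities that the article cites, about 10% to 20% remains at correlations of 0.3 to 0.4. This is a worthwhile improvement to a secondary analysis, not a flaw in the trial's main result.

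**What to change.** In the analysis plan:

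1. Take the outcome of the alliance analysis as YP-CORE at 12 and at 24 weeks only.
2. Report two models side by side: the planned baseline-adjusted model, and the same model with 6-week YP-CORE added.
3. Interpret the first as prediction. Describe alliance as a possible mechanism of later change only if the association persists in the second.
4. State the limits of the second model: it removes any true alliance effect already realised by week 6, and because YP-CORE is measured with error it reduces the bias without fully removing it.

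The cost is a few lines of wording and one extra model. No new data, visits or participants are needed.
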